## Abstract

**Abstract:**

**Introduction:**

Multimorbidity or the presence of two or more long-term conditions is now common in people undergoing surgery. However, current care pathways often miss these healthcare encounters to support long-term health promotion. Therefore, there is a need for practical, scalable approaches that can be integrated into routine surgical care, for which limited solutions exist at present. We have co-designed a structured preoperative checklist to help identify and manage long-term conditions in patients listed for elective surgery. This study aims to evaluate the feasibility and acceptability of this preoperative checklist in patients undergoing elective surgery.

**Methods and analysis:**

This is a mixed-methods feasibility study in one National Health Service trust in the UK. We will recruit up to 50 adults scheduled for elective surgery and use the checklist during initial surgical clinic appointments. Quantitative data will include recruitment and retention rates, completion of the checklist and baseline clinical characteristics, analysed using descriptive statistics. Qualitative data will be collected through semistructured interviews with up to 16 patients and clinicians. These interviews will be analysed thematically, guided by the Consolidated Framework for Implementation Research. Triangulation of quantitative and qualitative data will allow us to explore fidelity, acceptability, barriers and facilitators to implementation and refine the intervention ahead of a future pilot cluster randomised trial.

**Ethics and dissemination:**

This study has received approval from the Yorkshire & The Humber - Sheffield Research Ethics Committee (approval number: 25/YH/0045). All participants will give written informed consent. Results will be published in peer-reviewed journals and shared with participants, the public and policy stakeholders.

STRENGTHS AND LIMITATIONS OF THIS STUDYThe mixed-methods approach, combining quantitative and qualitative data, will provide a detailed understanding of the checklist’s practical implementation and acceptability to both patients and clinicians.We use prespecified progression criteria and a priori frameworks such as Reach, Adoption, Implementation and Maintenance for reporting, Carroll for fidelity and Weiners’ tool for acceptability to structure the feasibility evaluation.One of the limitations is this study is conducted in one National Health Service site with small sample sizes, but meaningful to gather learning ahead of wider evaluation.

## Introduction

 People are living longer, and, as a result, the number of people living with long-term health conditions such as cancer, diabetes and hypertension has increased rapidly over the past two decades.^1 2^ These conditions often occur together, known as multiple long-term conditions (MLTC) or multimorbidity. MLTC is now recognised as a major public health challenge, with 14 million adults in the UK living with MLTC.^3^,^5^ Projections suggest that the number of people affected will double or even triple in the next decade, especially among older adults.^6^ This rapid increase in the prevalence of MLTC poses challenges for health and care systems. Existing models of care, particularly in secondary care, are often designed around single diseases. This has led to fragmented and poorly coordinated care for people with MLTC, particularly during times when they are most vulnerable, such as around the time of surgery.^7^ Patients with MLTC have higher healthcare use and often experience poorer outcomes, including after surgery.^8^

Each year, 313 million people undergo surgery worldwide,^9^ and up to seven million in the UK alone.^10^ Surgery in people with MLTC is more complex, associated with higher risk and more expensive for health systems.^8^ Therefore, it is essential that the surgical journey delivers good short-term and long-term outcomes for these patients. Over the past decade, there have been advances in surgical pathways. For example, the orthogeriatric model has improved outcomes for patients undergoing surgery for hip fractures and has been adopted in many countries.^11 12^ However, similar models are infrequent in other types of surgery. Prehabilitation programmes, which prepare patients for surgery, exist, but are limited to a few centres and often focus only on the short preoperative period.^13 14^ Therefore, there is little attention paid to long-term holistic care and health promotion for people with MLTC in surgical pathways. As rates of MLTC continue to rise, especially in patients undergoing elective surgery, there remains a need for practical, scalable solutions that can be embedded into routine surgical care.^15^

To address this knowledge gap, we co-designed a preoperative checklist with key stakeholders such as patients, surgeons, anaesthetists, nurse specialists and geriatricians.^16^ This choice was informed by preparatory work: pathway mapping showed that preassessment often occurs late, leaving little time to optimise long-term conditions; a rapid scoping and a national survey suggested that screening for common conditions (eg, hypertension, diabetes) at the point of listing is uncommon; clinicians reported recognising MLTC but being unsure of the immediate next steps in busy clinics; beliefs varied about whether early optimisation was feasible and referral routes to primary care or specialist services were inconsistent.^16^ Patients and clinicians therefore prioritised a brief, structured tool to be used at the first surgical clinic after listing. The checklist brings guideline-based prompts together on one page, standardises the conversation and triggers clear actions (tests to request or retrieve, brief health-promotion advice and referrals or letters to primary care), without creating a new clinic. This checklist aims to address two linked problems: (1) surgery is a teachable moment to support long-term health for people with MLTC and (2) uncontrolled MLTC drives avoidable perioperative risk. Therefore, the ultimate impact is two-fold: (1) better long-term management and (2) fewer perioperative harms through earlier identification and action.

However, this checklist has not yet been tested in routine clinical practice. Before planning a larger pilot trial, it is important to understand if the checklist is feasible and acceptable to patients and clinicians and to identify potential barriers and facilitators to its use. Feasibility studies are an essential step in the development of complex interventions, allowing refinement of both the intervention and its implementation in real-world settings. The aim of this study is to assess the feasibility of implementing a structured preoperative checklist for health promotion and MLTC management in elective surgical patients in the National Health Service (NHS) (table 1). The primary objectives are to:

Determine the feasibility of the intervention, including recruitment, retention and completion rates;

**Table 1 T1:** Mapping of objectives of study to relevant quantitative and qualitative phase and measurement throughout study

	Measure	Cohort study	Interviews (patients)	Interviews (clinicians)	Source	RE-AIM framework
Objective 1: feasibility of study						
Recruitment	Proportion of eligible patients enrolled (screened → eligible → approached → consented)	Yes	–		Screening log	Reach
Retention or attrition	Proportion of patients completing follow-ups	Yes	–		Study log	Reach
Checklist completion, adherence	Per eligible clinic visit: REDCap record or scanned paper checklist linked to ID, cross-checked versus attendance list; plus item completion %	Yes	–		REDCap; PDFs; clinic log	Reach and adoption
Objective 2: evaluate acceptability and fidelity (patients and clinicians).						
Fidelity: dose	Counts of actions: tests, advice, referrals/signposting, primary care letter; verified in notes	Yes	–	Yes	Checklist; patient records	Implementation
Fidelity: quality/ competence	Proportion of completion of checklist actions against a predefined criterion	Yes	–	–	Audit tool	Implementation
Fidelity: participant responsiveness	Patient usefulness, understanding, actions started (3–5 items)		Yes		Patient questionnaire	Implementation
Acceptability or appropriateness	*Patients: AIM means; % ≥4/5* *Clinicians: AIM means; % ≥4/5*		Yes	Yes	Patient and clinician survey	Adoption and implementation
Objective 3						
Barriers to delivery	CFIR-guided interviews; matrix with quantitative signals		–	Yes	Interview notes	Adoption &and implementation
Objective 4						
Intervention maintenance	Maintenance of health promotion		Yes - 3 months and 6 months		Maintenance	
	Improved adherence to chronic disease and medications		Yes - 3 months and 6 months		Maintenance	
	Intervention maintenance	–	–	Yes - 2 months	Maintenance	
Objective 5						
Mechanisms	New diagnosis of MLTC-research notes	Yes	Yes - 3 months and 6 months		–	
	Follow-up in primary or secondary care-research notes	Yes	Yes - 3 months and 6 months		–	
Objective 6						
Acceptability of outcome measure	Multimorbidity burden treatment questionnaire: response rate; missingness; burden comments	0 months, 3 months and 6 months			–	Implementation

MLTC, multiple long-term conditions; RE-AIM, Reach, Adoption, Implementation, Maintenance.

Evaluate the acceptability and fidelity of intervention delivery to patients and clinicians;Understand barriers and facilitators to delivering the intervention and refine implementation strategies;Assess how well the intervention can be maintained within existing surgical pathways, including links to primary care;Explore how the checklist may influence current pathways and outcomes;Assess the acceptability of proposed outcome measures.

This feasibility study will use mixed methods to capture both quantitative outcomes (such as recruitment and completion rates) and qualitative insights from patients and clinicians. The findings will be used to refine the checklist and its implementation and to inform the design of a future randomised trial.

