**Figure 1 F1:**
[figure not shown]
A summary flow chart of the overall plan of the mixed-methods feasibility study.

**Table 2 T2:** Summary schedule of procedures for the mixed-methods feasibility study

	Time point			
	t_0_ (Surgical clinic)	t_1_ (1–2 months)	t_1_ (3 months)	t_2_ (6 months)
Enrolment				
Eligibility screen	x			
Patient consent (overall study)	x			
Patient consent (interview)	x			
Intervention				
Clinical use of checklist	x			
Assessments				
Baseline	x			
Follow-up and PROMs	x		x	x
Interview (clinician)		x		
Interview (patient)			x	

PROM, Patient Reported Outcome Measure.

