### Recruitment and consent process

Patients will be recruited via the NHS hospitals providing surgical specialty services across the UK. Patients attending upper or lower gastrointestinal surgical clinics will be screened for potential inclusion. Patients will be approached by a member of the direct care team, either a clinical nurse specialist or by a member of the surgical team. Recruitment will take place at a routine clinical visit. Patients will be provided with a copy of the study patient information sheet which will give full details of the study. Interested patients will be asked for consent for the clinical team to enter their contact details onto the secure REDCap data capture system^21^ hosted by the University of Birmingham. This initial collection of data is through implied consent. They will also be asked for consent for participating in an interview of up to 1 hour. They will then be contacted to answer any questions that they may have and to arrange a suitable time for the interview. Each participant will be allocated a unique identification number for the purposes of the study for the purposes of interview transcription. Participating sites will also be asked to display a poster advertising the study in appropriate waiting rooms. For the interviews with healthcare professionals, they will be recruited directly by the research team. They will also be asked for consent to participate in an interview of up to 1 hour and arrange a suitable time for the interview. Each participant will be allocated a unique identification number for the purposes of the study for the purposes of interview transcription. Participating sites will also be asked to display a poster advertising the study in appropriate waiting rooms. Prior to recruitment, patients will be provided with a patient information sheet and will be asked to complete a consent form for both the feasibility study and interview. The process for obtaining informed consent will be in accordance with Good Clinical Practice. The consent form must be completed before the scheduled time of the interview. Both the patient and clinician consent form is presented in onlinesupplemental files 3  4, respectively.

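### Tables 1 and 2 disagree on the 6-month patient interview, so the two patient-level Objective 4 measures have no stated 6-month source

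*Protocol article*

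**What the plan says.** The Introduction lists six primary objectives. The fourth is: "Assess how well the intervention can be maintained within existing surgical pathways, including links to primary care". The Outcomes section says that Table 1 sets out the measures, sources and timing for each objective. The Study design and setting section presents Table 2 as the detailed schedule of procedures.

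- **Table 1, Objective 4, patients.** There are two measures: maintained health promotion, and "Improved adherence to chronic disease and medications". For both, the cohort cell is blank and the patient-interview cell reads "Yes - 3 months and 6 months".
- **Table 1, Objective 4, clinicians.** There is one row, on maintenance of the intervention, at 2 months.
- **Table 1, Objective 5.** The two rows (new diagnoses; follow-up in primary or secondary care) have the same patient-interview entry, and the cohort column also says yes.
- **Table 2.** The patient interview is marked once, at 3 months. The clinician interview is marked once, at 1–2 months. The only entry at 6 months is "Follow-up and PROMs", which is also marked at the surgical clinic visit and at 3 months.
- **Data collection and management.** Baseline data are demographics, smoking status, past medical history and the treatment burden questionnaire. Clinic visits record new diagnoses and follow-up care, and checklist completion is monitored.

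**The concern.** Both tables are meant to fix timing, and they fix it differently for a primary objective. Whoever runs the study from Table 2 will not hold a 6-month patient interview. Whoever writes the report from Table 1 will expect one. Because maintenance is about what lasts, the later time point carries most of the information, and it is the one that disappears.

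Two related weaknesses affect how the same rows can be read. A measure called improved adherence needs something to improve from, and an item not asked at the first clinic visit cannot be collected prospectively later. A single early clinician time point may also describe use of the checklist while the study's own prompts are in place, which is different from use within existing pathways.

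**Working it through.** The plan gives no figure to reproduce, so the check sets the two tables side by side and adds simple calendar arithmetic.

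**1. Patient interview time points**

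| Table 1 row | Cohort source | Patient interview, Table 1 | Patient interview, Table 2 | Stated 6-month source if Table 2 is followed |
|---|---|---|---|---|
| Obj. 4: health promotion maintained | blank | 3 and 6 months | 3 months | none |
| Obj. 4: improved adherence | blank | 3 and 6 months | 3 months | none |
| Obj. 5: new diagnoses | yes | 3 and 6 months | 3 months | cohort data |
| Obj. 5: follow-up care | yes | 3 and 6 months | 3 months | cohort data |

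Four rows carry the mismatch. Two of them lose their only stated 6-month source. For those two, 1 of 2 planned time points remains.

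**2. Does the 6-month contact fill the gap?** Table 2 has a follow-up and patient-reported outcome contact at 6 months. The only patient-reported outcome named for it is the treatment burden questionnaire (Objective 6: 0, 3 and 6 months). The visit data listed are new diagnoses and follow-up care. Neither Objective 4 measure is among them.

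**3. Adherence baseline.** The adherence row lists 3 and 6 months. The Objective 6 row lists 0, 3 and 6 months, so the table does show a baseline where one is intended. Adherence is not among the listed baseline data. The checklist prompts cover current treatments and medicines reconciliation, and adherence itself is not named.

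**4. Clinician time point.** Recruitment lasts 3 months. The origin of the 2 months is not defined for clinicians.

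- From study launch: 3 − 2 = 1 month of recruitment remains when the question is asked.
- From each patient's clinic visit (the origin of Table 2): patients enrol from month 0 to month 3, so the point falls between month 0 + 2 = 2 and month 3 + 2 = 5. It precedes the close of recruitment only for patients enrolled in the first month, about 1/3 if accrual is even (an assumption).

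On either origin, no clinician contact is scheduled later than 2 months after it.

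**The case against.** The strongest reply is that the patient-interview column in Table 1 is not used strictly for interviews. It also holds participant responsiveness, whose source is a patient questionnaire, and acceptability, whose source is a survey. The 6-month entry may therefore mean patient-reported data at the 6-month contact that Table 2 already has. The Objective 4 rows also show a RE-AIM domain in the source column, so cell positions should be read with care. This stands as a possible explanation. It would make the defect one of labelling, but the two measures are still absent from the data listed for that contact.

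Other replies limit how far the point goes:

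- **Objective 4 cannot be answered.** A reader might infer this, but the documents do not support it. The 3-month interviews remain, checklist completion is logged per eligible clinic visit, and where a review is planned the checklist may be revisited within 6 months to record progress.
- **Clinicians are asked while recruitment is still running.** This follows only if the 2 months run from launch. The Study design and setting section says that interviews take place during and after the study period, without giving a month. Champion support lasts only the first fortnight, so some use after it is observed, although the prompts apply during the study period.
- **Change in adherence is lost for all 50 patients.** The measure belongs to interviewed patients, who are part of a planned 16 patients and clinicians combined. Patients can describe change in retrospect, no hypothesis test is planned, and the topic guides and questionnaire items are in supplements not shown.
- **Consent covers only one interview.** The text reads "They will also be asked for consent for participating in an interview of up to 1 hour". That limits duration and does not settle the number of interviews.

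**Conclusion.** The contradiction between the tables is real and needs correcting. If Table 2 is followed, two measures of a primary objective have no stated 6-month source. The two Objective 5 rows share the inconsistency with little harm, since their cohort data remain.

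The adherence wording is a smaller fault: the label promises change and the article lists no baseline for it. The article's baseline list may not be exhaustive, so this rests on the text shown. The clinician time point is a fault of definition first. It becomes a fault of timing if the origin is launch, which is the more natural reading for clinicians but is not stated.

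Severity is moderate. The evidence is descriptive, and Objective 4 stays partly answerable.

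**What to change.** 1. Make Tables 1 and 2 agree. The cheapest way is to collect the health-promotion and adherence items at the 3- and 6-month follow-up contacts that Table 2 already schedules, mark the cohort column in Table 1 accordingly, and keep the single 3-month interview. If a 6-month interview is truly intended, add it to Table 2.
2. Ask the same adherence items at the first clinic visit, or relabel the measure as self-reported or patient-perceived adherence.
3. State the origin of the clinician 2-month point. If it is launch, ask the maintenance question after recruitment and study prompts have ended.

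The cost is a few extra questionnaire items at existing contacts, possibly a later date for one clinician question, and a minor amendment. The baseline item is the urgent part, because it has to be in place before patients attend their first study clinic.

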## Methods and analysis

### Study design and setting

This pilot and feasibility study is a non-randomised study, and all participants will receive the intervention. The pilot and feasibility study will be consistent with guidance proposed by Eldridge *et al*^17^ and O’Cathain *et al*^18^ and reported using the adapted Standard Protocol Items: Recommendations for Interventional Trials^19^ reporting template for feasibility studies (online supplemental file 1). A mixed methods approach will be undertaken to assess the feasibility of the preoperative checklist, drawing on principles from the National Institute of Health Research and Medical Research Council Complex intervention framework (figure 1).^20^ The study will take place in one large NHS hospital site, University Hospital Birmingham NHS Trust. The preoperative checklist will be implemented in surgical clinics at hospitals within the trust, and follow-up data will be collected as part of routine care. The planned study period is from September 2025 to December 2025. Recruitment will take place over 3 months, with follow-up continuing for up to 6 months post enrolment. Qualitative interviews will be conducted during and after this period, with data analysis taking place alongside data collection and following study completion. A detailed schedule of procedures is presented in table 2.

**Figure 1 F1:**
[figure not shown]
A summary flow chart of the overall plan of the mixed-methods feasibility study.

**Table 2 T2:** Summary schedule of procedures for the mixed-methods feasibility study

	Time point			
	t_0_ (Surgical clinic)	t_1_ (1–2 months)	t_1_ (3 months)	t_2_ (6 months)
Enrolment				
Eligibility screen	x			
Patient consent (overall study)	x			
Patient consent (interview)	x			
Intervention				
Clinical use of checklist	x			
Assessments				
Baseline	x			
Follow-up and PROMs	x		x	x
Interview (clinician)		x		
Interview (patient)			x	

PROM, Patient Reported Outcome Measure.

### Patient and public involvement

Patients were involved in commenting on and reviewing the initial application to the University of Birmingham. Together with patients and public group and expert clinician group, who were involved at the outset of the NIHR funding application, they have iteratively designed this feasibility study. For this part of the study, patients have been involved in designing the topic guide and the patient lead will be involved to review the coding framework from the interviews. They will also work with them to produce a lay summary of the results for dissemination to study participants.

### Intervention

The intervention consists of a structured preoperative checklist, which has been co-designed with patients, surgeons, anaesthetists, nurse specialists and geriatricians.^16^ The checklist is a brief, clinician-delivered tool used during the surgical clinic that integrates five components: (1) early identification prompts (diagnosed conditions, current treatments, recent Blood pressure (BP), Haemoglobin 1AC (HbA1c) where relevant, smoking, alcohol, physical activity, weight/body mass index, frailty indicators) to surface long-term health needs at the first post-listing contact; (2) action prompts aligned to guidance (eg, request or retrieve recent tests; confirm accurate BP; consider HbA1c if diabetes is suspected; reconcile medicines; flag polypharmacy concerns) so that the discussion leads to specific next steps; (3) brief health promotion advice on smoking and weight management to structure a short, patient-centred conversation and agree one achievable action; (4) coordination triggers to standardise onward care (tick-box referrals/signposting to primary care or specialist services and an auto-templated letter to primary care summarising agreed actions, tests and responsibilities) and (5) follow-up flag to revisit the checklist within 6 months where a review is planned, recording actions completed and any barriers. Key materials include a one-page paper (tick-boxes plus brief free text for the plan) and a local referral directory (primary care advice and guidance, specialist clinics, community services). The checklist promotes health-related discussion by scripting key topics and supports coordination by generating a short, standardised plan and primary care letter during the same visit, without creating a new clinic or lengthening the pathway. The template checklist is presented in online supplemental file 2.

The checklist is intended for all adult patients (≥18 years) listed for elective upper or lower gastrointestinal surgery who attend participating surgical clinics during the study period. Exclusions are day-case minor procedures that do not involve a preoperative assessment, non-elective/emergency presentations and patients unable to consent in English without an interpreter when none is available (sites may include translated materials where feasible). Clinicians are prompted to use the checklist at the first clinic visit after listing (‘post-listing clinic’) via a sticker on the printed clinic list, an EHR banner or smart-phrase where available and the REDCap start page. Use is strongly encouraged as part of routine documentation; non-use and the reason (eg, urgent add-on, interpreter delay, clinic over-run) are recorded. Where a review is planned, the checklist may be revisited at a subsequent follow-up clinic within 6 months to document progress on agreed actions. The checklist is delivered by the surgical team, usually a consultant surgeon or clinical nurse specialist, after a 60 min orientation covering purpose, components, worked cases and how to record and communicate the plan; a local clinical champion is available for on-the-shoulder support during the first fortnight.

